### Sample size

Since this intervention is being rolled out programmatically, the sample size will not be capped. Using camp data from 2022, we calculated a mean of 0.88 B+ diagnosed per camp with an over dispersion of 1.34. We calculated intra-cluster correlation (ICC) of 0.12 using one-way analysis of variance (ANOVA) of B+ and van-clusters. We subsequently used ‘*The Shiny CRT X Calculator: Power and Sample size for Cluster Randomised Trials Test*’ to conduct the sample-size calculation for stepped-wedge trial using a cross-sectional sampling structure assuming an exchangeable correlation structure and significance level of 0.05.^23^ We anticipate each van to conduct approximately 10–13 camps per month (cluster-size), accounting for exclusion of camps in districts without Xpert testing and cancellations of camps due to external factors. With 10 steps and three vans switching per cluster, the trial is powered at 80% to detect a 20% increase in B+ in the intervention arm assuming an average of 10 camps per month or 3300 total camps over the study period. A power of 90% is achieved if 13 camps per month are undertaken during the study period or 4290 total camps over the study period.

### Statistical analysis plan

Frequency statistics will be used to describe the baseline characteristics of camps and the participants (box 1). These will be compared between the intervention and control arms to assess the appropriateness of the randomisation process and tested for statistical significance using parametric and non-parametric tests as appropriate.

The primary analysis will use a Poisson generalised liner mixed regression using the number of bacteriologically positive TB diagnosed per camp as the outcome variable. This may be modified to a mixed negative binomial regression, depending on the dispersion of data and model goodness of fit. To account for clustering of outcomes within the randomisation unit (van-teams), they will be added as a random effect in the model. Due to secular trends in the incidence of TB, a fixed effect for time (monthly) will be added into the model, based on the trend in B+ reported. TB notifications are typically higher in the summer months in Pakistan; however, it is unclear whether this is due to health-seeking behaviour or disease pathophysiology. Camps will be categorised into intervention or control based on their exposure to the MATCH-AI intervention and added as a binary explanatory variable into the model to calculate the incidence rate ratio between the two arms. The primary analysis will be intention-to-treat where all camps will be considered to have switched to the intervention group after their assignment, regardless of whether those camps were conducted using MATCH-AI. In the per-protocol analysis, only camps conducted at the location identified by the MATCH-AI software will be included. Camps conducted within a 2-km radius of the intended camp site (validated using GPS coordinates) will be included in the per-protocol analysis. A subgroup analysis will be carried out by stratifying the effect of the intervention over regional prevalence estimates of TB (high, medium, low) identified through a retrospective analysis of mobile X-ray-based camps in Pakistan conducted prior to the start of the trial.

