### Randomization

The unit of randomisation in this trial will be a mobile X-ray unit and its associated team members (van-team). Since van-teams are shared between districts, it is more appropriate to randomise the teams instead of individual districts. The number of districts covered by each van-team varies from 1 to 3 depending on the size and population of the districts. A total of 30 van-teams will be randomised to the intervention through a computer-generated list at the start of the trial. The randomisation process and schedule will be carried out independently by the research team. Van-teams will be masked to the intervention allocation and randomisation schedule until they switch to the intervention.

The total proposed length of the study is 12 months (data collection period). At the start of the trial, no clusters will be using MATCH-AI. A 2-month pre-rollout period will be used to collect baseline control data and conduct pilot testing of the intervention. From month 3 onwards, three van-teams will be randomly selected to start using MATCH-AI for camp selection (figure 1). By the end of the trial, all 30 teams will be using MATCH-AI for camp planning.

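### The primary model and the power calculation both assume that a van-team's yield correlation does not fade from month to month; this is untested, and if it fades the 5% test is too liberal and the 80%/90% power too high

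*Protocol article*

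**What the plan says.** Statistical analysis plan section: the primary analysis is a mixed Poisson regression of bacteriologically confirmed cases per camp, with a binary intervention term and a fixed effect for month. On clustering it says "To account for clustering of outcomes within the randomisation unit (van-teams), they will be added as a random effect in the model". No other random effect is named. On distribution it adds "This may be modified to a mixed negative binomial regression, depending on the dispersion of data and model goodness of fit".

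Sample size section: power was computed with a "cross-sectional sampling structure assuming an exchangeable correlation structure and significance level of 0.05". The inputs are described as follows: "we calculated a mean of 0.88 B+ diagnosed per camp with an over dispersion of 1.34", and "We calculated intra-cluster correlation (ICC) of 0.12 using one-way analysis of variance (ANOVA) of B+ and van-clusters". The claim is that "the trial is powered at 80% to detect a 20% increase in B+ in the intervention arm" with 10 camps per van-month (3300 camps), rising to 90% with 13 (4290 camps).

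Randomization section: "The number of districts covered by each van-team varies from 1 to 3 depending on the size and population of the districts".

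**The concern.** In a stepped wedge much of the information on the effect comes from each van's change between months. The Discussion gives this as a reason for the design, since clusters first serve as their own controls. A van intercept captures what is constant about a van, and a common month effect captures what is shared by all vans. Neither captures a good or bad month specific to one van. Such variation enters the effect estimate but not its model-based standard error, so intervals are too narrow and false positives too frequent. Power computed without it is too high.

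The article gives reasons to expect some of it. A van may serve up to three districts. Control camp plans are approved monthly and intervention site lists are sent monthly (Current standard of care; Study intervention). The Discussion expects logistical problems and external disruptions. The 2022 ICC cannot settle the matter, because a one-way ANOVA by van pools pairs of camps from the same month with pairs from different months.

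At stake is the primary p-value of a trial meant to inform a national policy on site selection.

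**Working it through.** **Inputs from the article.** 30 van-teams; 10 steps of 3 vans; m = 10 or 13 camps per van-month; mean 0.88; overdispersion 1.34; ICC ρ = 0.12; a 20% increase, so the difference is 0.20 × 0.88 = 0.176; α = 0.05.

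**Assumptions.** Two-sided test; categorical months; 0.12 taken as the within-month ICC; 1.34 read as a variance-to-mean ratio, so σ² = 1.34 × 0.88 = 1.179. CAC is not given and is varied. The layout has 11 periods, because 30 × 11 × 10 = 3300 and 30 × 11 × 13 = 4290.

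**Variance model for van-month means (nested exchangeable).** For one van over T = 11 periods:

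V = σ²[ρ(CAC·J + (1 − CAC)·I) + ((1 − ρ)/m)·I]

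Here J is the matrix of ones and I the identity. The standard error (SE) of the effect is the square root of the treatment element of (Σ D′V⁻¹D)⁻¹, where D holds the period indicators and the treatment indicator.

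**Step 1: reproduce the stated power (CAC = 1).** SE = 0.0604 (m = 10) and 0.0533 (m = 13). For m = 10, 0.176/0.0604 = 2.91.
- t reference with 28 df: 80.2% and 89.0%.
- Normal reference: 82.9% and 91.0%.

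The stated 80%/90% is recovered. With a plain Poisson variance of 0.88 the normal reference gives 92.1% and 96.9%. With 1.34 as a negative binomial parameter (variance 0.88 + 1.34 × 0.88² = 1.918) it gives 62.7% and 73.5%. Neither matches, so overdispersion is already in the power figure and month-to-month van variation is not.

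**Step 2: power when CAC is below 1 and the model allows for it.**

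| CAC | m = 10 (t to normal) | m = 13 (t to normal) |
|---|---|---|
| 1 | 80.2% to 82.9% | 89.0% to 91.0% |
| 0.95 | 77.8% to 80.7% | 86.5% to 88.7% |
| 0.9 | 75.5% to 78.5% | 84.0% to 86.4% |
| 0.8 | 71.2% to 74.4% | 79.2% to 81.9% |

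**Step 3: type I error of the van-intercept model when CAC is below 1.** The fitted model takes the between-van variance as σ²ρ·CAC and treats the rest as independent camp noise. Its reported SE is compared with the true SE of the same estimator:

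type I error = 2Φ(−1.96 × reported SE / true SE)

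Worked case, CAC 0.8, m = 10:
- Van-by-month variance: 0.2 × 0.12 × 1.179 = 0.0283.
- Camp-level variance of a van-month mean: 0.88 × 1.179/10 = 0.1038.
- True month-level variance: 0.1038 + 0.0283 = 0.1321.
- The model spreads the extra part over the 10 camps: 0.1038 + 0.0028 = 0.1066.
- Resulting SEs: 0.0609 reported, 0.0674 true.
- 2Φ(−1.96 × 0.0609/0.0674) = 2Φ(−1.77) = 7.7%.

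| CAC | reported / true SE, m = 10 | type I error | reported / true SE, m = 13 | type I error |
|---|---|---|---|---|
| 1 | 0.0604 / 0.0604 | 5.0% | 0.0533 / 0.0533 | 5.0% |
| 0.95 | 0.0606 / 0.0623 | 5.7% | 0.0534 / 0.0555 | 5.9% |
| 0.9 | 0.0607 / 0.0641 | 6.3% | 0.0535 / 0.0575 | 6.8% |
| 0.8 | 0.0609 / 0.0674 | 7.7% | 0.0537 / 0.0614 | 8.6% |

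Simulation of the mixed model at 10 camps with dispersion handled (1,000 runs, simulation error about 0.7 to 1.3 points) gave 5.2% at CAC 1, 4.9% at 0.95 and 8.3% at 0.8. If correlation decays each month instead, the loss is larger: at a monthly factor of 0.95, type I error is about 10.0% / 11.5% and power 68.0% / 76.3% (t).

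**Step 4: the distribution.** Of σ² = 1.179, the share left within vans is 0.88 × 1.179 = 1.038, which is 1.18 times the mean. If Poisson were kept against that, simulated type I error at 10 camps was 7.1% at CAC 1 and 10.6% at CAC 0.8.

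**The case against.** **No CAC is given, and the grounds for a value below 1 are indirect.** This stands. A camp is one day's activity, so part of the spatial heterogeneity is camp-level noise. Serving several districts lowers CAC only if a van's sites cluster by month, and the article does not describe rotation. Repeat camps at the same site are allowed, and shocks shared by all vans go into the month effect. A reader might infer that the test certainly runs well above 5%; the document does not support that. At CAC 0.95 the inflation is under one point.

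**Overdispersion is not ignored.** This also stands. A reader might infer otherwise from the Poisson default, but the plan allows a negative binomial, and the stated power reproduces only with 1.34 included. Nor does 1.34 contradict a mixed Poisson outright: with an ICC of 0.12, the van effect alone gives a variance-to-mean ratio of 1/0.88 = 1.14. What remains is that the switch is discretionary although the planning data already showed overdispersion. A negative binomial would not cure the main problem, because it adds independent camp-level variance and no correlation within a van-month.

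**The power loss depends on the layout.** With 12 months, two of them baseline, and a normal reference, power is 85.0% / 92.5% at CAC 1, 80.6% / 88.3% at 0.9 and 76.5% / 83.9% at 0.8. On that grid 80% survives CAC 0.9. The stated camp totals, however, correspond to 11 periods. Camp numbers are also not capped, which may soften the loss.

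**A condensed article may leave variance components to a fuller plan.** It may, but this one states both the random effect and the exchangeable structure behind the power, and the two agree on CAC = 1.

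**Conclusion.** The concern holds in a conditional form. The stated primary model and power calculation both fix CAC at 1, and nothing in the article tests that. For any CAC below 1 the direction is certain: the test is anti-conservative and the stated power optimistic. The size is modest near 1 and material by 0.8, where type I error is about 8% to 9% and power about 71-74% / 79-82% in place of 80%/90%.

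These figures rest on the assumed CAC values, on 0.12 as the within-month ICC, on 1.34 as a variance-to-mean ratio and on the 11-period layout. If 0.12 is instead a blend of same-month and different-month pairs, the within-month ICC would lie somewhat above it and the effect would be slightly larger. The distribution rule is a secondary point.

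**What to change.** 1. Add a van-by-month random effect (nested exchangeable) to the primary model, or a structure in which correlation decays with time.
2. Estimate within-month and between-month ICCs from the 2022 camp data already held, use them to choose between the two structures, and restate power over a range of CAC that includes the estimate.
3. Name the negative binomial as the primary distribution in place of the optional switch.

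The cost is a change of analysis wording, one analysis of existing data and one re-run of the power calculation. The downside is slightly wider intervals and a lower stated power. If CAC is in fact 1, the added variance component will be estimated near zero and little is lost.

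### The stated primary model makes no use of each van's 2022 yield; one pre-randomisation covariate could add precision at almost no cost, by an amount the documents cannot fix

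*Protocol article*

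**What the plan says.** The Statistical analysis plan section sets a Poisson mixed model for bacteriologically confirmed TB per camp, with negative binomial as the alternative. Its stated terms are a van-team random effect ("To account for clustering of outcomes within the randomisation unit (van-teams), they will be added as a random effect in the model"), a monthly fixed effect and a binary intervention term. No baseline covariate is named.

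The Sample size section draws on earlier camps: "Using camp data from 2022, we calculated a mean of 0.88 B+ diagnosed per camp with an over dispersion of 1.34". The same section groups yield by van: "We calculated intra-cluster correlation (ICC) of 0.12 using one-way analysis of variance (ANOVA) of B+ and van-clusters". For 10 camps per van each month, 3300 in all, it claims that "the trial is powered at 80% to detect a 20% increase in B+ in the intervention arm". For the larger target it says: "A power of 90% is achieved if 13 camps per month are undertaken during the study period".

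In the analysis, pre-trial camps are used only to define regional prevalence subgroups, "identified through a retrospective analysis of mobile X-ray-based camps in Pakistan conducted prior to the start of the trial".

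**The concern.** Vans differ a lot. Taking the total variance as 1.34 × 0.88, an ICC of 0.12 gives a between-van standard deviation of √(0.12 × 1.34 × 0.88) = 0.376. Against a mean of 0.88 this is a coefficient of variation of about 43%. The Discussion itself calls the ICC high.

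A stepped wedge estimate combines within-van and between-van comparisons. The random intercept gives the between-van part little weight when van levels vary widely. A covariate that explains part of that variation lets the between-van part contribute more. It also adjusts for a chance link between van yield and switch order, which matters with only 30 vans, three per step, and no balancing described. The first vans to switch have at most two control months in the trial, and those months also serve for pilot testing.

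The covariate is measured before allocation, so adjusting for it introduces no confounding. What is at stake is the width of the interval for the rate ratio.

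**Working it through.** **Inputs from the article.** 30 vans, 10 steps, three vans per step; control mean 0.88; overdispersion 1.34; ICC 0.12; a 20% increase, so a difference of 0.2 × 0.88 = 0.176; alpha 0.05 (sidedness not stated, taken as two-sided); exchangeable correlation. The 3300 camps equal 30 × 11 × 10, so the calculation used 11 periods.

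**Assumptions not in the article.** About 120 camps per van in 2022, and a correlation c between a van's true level in 2022 and in the trial.

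**Variance components.**
- Mean over arms: (0.88 + 1.056)/2 = 0.968. Total variance: 1.34 × 0.968 = 1.297.
- Between-van: τ² = 0.12 × 1.297 = 0.1557. Within-van: 1.297 − 0.1557 = 1.1415.
- Per van-month at 10 camps: σ² = 1.1415/10 = 0.11415.

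**Variance of the effect (Hussey-Hughes).**

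Var = Kσ²(σ² + Pτ²) / [(KU − W)σ² + (U² + KPU − PW − KV)τ²]

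Here K = 30, P = 11, U = 165, W = 3465 and V = 1155. So KU − W = 1485, and the τ² coefficient is 27225 + 54450 − 38115 − 34650 = 8910.

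**Reproducing the stated power.**
- Numerator: 30 × 0.11415 × (0.11415 + 11 × 0.1557) = 6.254.
- Denominator: 1485 × 0.11415 + 8910 × 0.1557 = 1556.4.
- Var = 0.004018, standard error 0.0634, z = 0.176/0.0634 = 2.776.
- Power = Φ(2.776 − 1.960) = 79.3%, against 80% stated.
- At 13 camps the same steps give 88.3%, against 90% stated.
- With 12 periods (two baseline months plus ten monthly steps) the figures are 81.5% and 90.0%.

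**Adding the covariate.** Reliability of a 2022 van mean from n camps is n × 0.12 / [1 + (n − 1) × 0.12], which is 0.942 at n = 120. The covariate explains R² = c² × 0.942 of the between-van variance, so τ² becomes τ²(1 − R²). At c = 1, τ² falls to 0.00896 and Var = 0.7286/249.4 = 0.002921, a ratio of 0.727. The last column is the number of camps beyond 3300 that the model without the covariate would need for the same variance.

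| c | R² | Variance ratio | Power | Equivalent camps |
|---|---|---|---|---|
| 0.3 | 0.085 | 0.996 | 79.5% | 15 |
| 0.5 | 0.236 | 0.986 | 79.8% | 49 |
| 0.6 | 0.339 | 0.977 | 80.2% | 80 |
| 0.8 | 0.603 | 0.939 | 81.7% | 223 |
| 0.9 | 0.763 | 0.889 | 83.8% | 431 |
| 1.0 | 0.942 | 0.727 | 90.3% | 1,300 |

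**Sensitivity.**
- With 60 camps per van in 2022 (reliability 0.891), the gain is about 197, 359 and 870 camps at c = 0.8, 0.9 and 1.0.
- With 12 periods and 120 camps in 2022, it is about 195, 379 and 1,174.
- If van effects decay by month and 2022 is treated as 12 earlier months, a monthly correlation of 0.95 saves about 260 camps with no gap before the trial and about 70 with an assumed 8-month gap. At 0.90 the savings are about 150 and 17.
- Simulated Poisson mixed models (400 to 450 per setting) gave variance ratios of 0.74 and 0.83 (two runs) at c = 1.0, and 0.93, 0.95 and 0.97 at 0.9, 0.8 and 0.6. The direction agrees with the formula; the gains are mostly smaller.

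**The case against.** The strongest reply is that precision covariates are a detail which a condensed article leaves to a full analysis plan. On this view the article never says that its listed terms are the only ones, and the Discussion promises adjustment for other confounders. This does not dispose of the point. The article sets out the primary model term by term, and the Discussion sentence concerns confounders and secondary analyses. A fuller plan may add the covariate, but it would then differ from the model stated here.

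Other parts of the reply stand. The van random effect and the own-control comparison already remove most between-van noise, which is why the gain is small over much of the range. The sample size is not capped, and the article's own span of 3300 to 4290 camps is wider than most of the gains in the table. Two simulation results are weaker than the formula: ratios of 0.83 and 0.93 correspond to about 710 and 260 camps.

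A reader might infer that the covariate is worth at least a couple of hundred camps, and up to 1,200. The documents do not support that as an unconditional range. They give neither the 2022-to-trial correlation nor the number of 2022 camps per van, and 200 is not a floor. The top end needs almost perfect persistence. The power calculation was done "assuming an exchangeable correlation structure and significance level of 0.05", but that describes the trial periods; carrying it back to 2022 is a further step.

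Nor does the article show that the same 30 van-teams and districts are all in the 2022 data. That is likely, not established.

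**Conclusion.** The point holds as a missed gain in precision. The stated primary model leaves out a prognostic, pre-randomisation, van-level measure that the authors were in a position to compute. It would be wrong to infer that the trial is biased, misanalysed or underpowered on this account: the stated power is met, within two percentage points, without the covariate.

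The size is conditional. With about 120 camps per van in 2022, 11 periods and 10 camps per van-month, the gain runs from about 50 camps at a correlation of 0.5 to about 1,300 at 1.0, and is near zero if van yields drift. With 60 camps per van in 2022 the top figure is about 870. The change is worth making because little is lost if persistence is weak, while strong persistence would bring power at 10 camps per month close to what the article expects from 13.

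**What to change.** Add one van-level fixed covariate to the primary model: the log of the van's mean B+ per camp in 2022, computed from the trial's eligible districts and frozen before month 1. For a van without 2022 data, use the mean of its districts. Keep the van random intercept, the month effects and the arm term. Report the model without the covariate as a sensitivity analysis.

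State how many of the 30 vans have 2022 data and how many camps each contributes. If the pre-trial camps span enough time, check how stable van yields are between earlier and later months, and quote the expected gain on that basis.

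The cost is one sentence in the plan, one derived variable and one degree of freedom among 30 vans, plus the work of restricting the 2022 records to eligible districts. No extra camps are needed.

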### Study intervention

#### Overview of MATCH-AI

The primary intervention in this study is the roll-out of MATCH-AI, an artificial intelligence software that models subdistrict TB prevalence. This software will be used to guide site selection of ACF camps. The software has been developed by the KIT Royal Tropical Institute in the Netherlands and Epcon, a commercial software firm.^22^ The MATCH-AI tool uses a Bayesian modelling approach to predict TB prevalence to a resolution of 10 000 population polygons. The model integrates data from a range of sources including historical TB facility notification data, previous ACF data as well as contextual factors such as demographics, income, population density, health indicators such as vaccination coverage and climate-related variables to predict localised TB prevalence. The software features a dashboard that allows for field staff to visualise maps that overlay TB prevalence and to help identify camp locations. The platform is self-learning and incrementally improves the prediction as further data is entered into the system.

In the intervention arm, camps will be conducted primarily in locations guided by MATCH-AI. Van-teams will be provided with a list of the highest predicted TB prevalence polygons (using street addresses and GPS coordinates) in each district as predicted by MATCH-AI. Van-teams will themselves not use the software interface. Instead, locations will be communicated by the Mercy Corps head office (via monthly emails) and van-teams will be instructed to move sequentially through this list to conduct ACF activities, starting with locations with the highest predicted prevalence. Once van-teams have switched over to the intervention group, they will continue to use MATCH-AI to guide their decision-making through to the end of the trial. Teams that are scheduled to receive the intervention will be provided with the list of locations 15 days prior to the start of the month, allowing sufficient time for them to transition to the intervention and to plan their community engagement activities. Van-teams will have the option to repeat camps at the same locations should they provide high yields. However, they will be encouraged to also screen additional locations within the list. A minimum (unspecified) number of camps will be allowed independent of the MATCH-AI predictions due to any prior commitments of van-teams with local communities or due to logistical constraints in reaching AI-directed sites.

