#### Current standard of care

In the control arm, field teams will continue to use existing approaches towards camp site selection. While not using software to guide decision-making, field staff may include targeting in their approach towards site selection. This is based on local knowledge, field experience from previous camps, analysis of historical data in paper-based TB registries and consultations with local stakeholders such as district TB coordinators and health officers. Camp plans are approved by the head office each month after reviewing recommendations of the district teams. Camp sites are often focused in slum dwellings and occasionally target key populations such as injection drug users. In addition, camps are often conducted in collaboration with local non-profits and private healthcare facilities such as general practitioner (GP) clinics. However, the current approach of camp site selection does not systematically use geographical targeting or quantitative methods to identify TB hotspots.

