A limitation of the trial design is that field staff will not be masked to the intervention status once they have switched over from the control group. Another limitation inherent in the design is that van-teams will conduct a certain proportion of camps in locations independent of the MATCH-AI recommendation. This reflects a pragmatic compromise whereby teams will be able to retain some autonomy in the selection of a camp due to commitments with local partners such as private GPs, non-governmental organisations and community groups. These camps have been retained in the primary analysis to make the results more externally generalisable as programmes would likely encounter such practical considerations. The per-protocol analysis will exclude these camps and will provide a direct estimate of the intervention effect. We anticipate the trial implementation to be affected by logistical challenges common in programmatic implementation such as sputum collection and testing, data reporting accuracy and external disruptions. A randomised evaluation will help ensure that these constraints do not bias results towards either the intervention or control arms whereas appropriate statistical methods and secondary analyses will adjust for other confounders. A potential limitation of the stepped wedge design is that secular trends in TB incidence may affect outcomes between intervention and control groups. This will be adjusted for using a fixed effect for time (monthly) in the regression models. An extensive staff training and capacity-building programme along with monitoring will help minimise data collection and reporting errors. An electronic data-collection tool will be concurrently rolled out to support long-term capacity for research within the implementing partners in Pakistan.

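### The per-protocol analysis removes non-randomly selected camps from the intervention phase only, so it cannot be called a direct estimate of the software's effect

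*Protocol article*

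**What the plan says.** The primary analysis is intention-to-treat: "all camps will be considered to have switched to the intervention group after their assignment, regardless of whether those camps were conducted using MATCH-AI". The per-protocol set is then defined in the same section: "In the per-protocol analysis, only camps conducted at the location identified by the MATCH-AI software will be included". A tolerance follows: "Camps conducted within a 2-km radius of the intended camp site (validated using GPS coordinates) will be included in the per-protocol analysis".

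The Discussion explains which camps are meant. After describing camps held away from the software's recommendation, it says: "The per-protocol analysis will exclude these camps and will provide a direct estimate of the intervention effect".

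Two places say why such camps occur. Overview of MATCH-AI states: "A minimum (unspecified) number of camps will be allowed independent of the MATCH-AI predictions due to any prior commitments of van-teams with local communities", and adds logistical difficulty in reaching the listed sites. The Discussion says teams keep some autonomy "due to commitments with local partners such as private GPs, non-governmental organisations and community groups".

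For the control phase, Current standard of care says that "camps are often conducted in collaboration with local non-profits and private healthcare facilities such as general practitioner (GP) clinics". No rule removes these camps from the per-protocol comparison.

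**The concern.** A camp can be off-list only once there is a list, that is, after its van has switched. The exclusion therefore acts on the intervention phase alone. What it removes is defined by circumstances that may well relate to yield: a standing commitment to a partner, or a listed site that could not be reached. The same kind of partner-linked camp remains among the controls. The result compares a selected set of intervention camps with an unselected set of control camps.

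The planned model does not repair this. The van random effect and the month fixed effect absorb differences between vans and between months. The selection happens camp by camp within a van-month.

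The stake is interpretation. Off-list camps pull the intention-to-treat ratio away from what full adherence would give. If the primary result is weak, a reader will look to the per-protocol result, which the protocol has already described as direct. It does not have the protection of randomisation that this description suggests.

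**Working it through.** **1. The plan's own figures.** The document gives no figure for the per-protocol analysis. The yardstick is the design effect in Sample size: a 20% increase (ratio 1.20), with 80% power at 10 camps per van-month and 90% at 13. A Hussey-Hughes calculation (30 vans, 10 sequences of 3, 11 periods, exchangeable ICC 0.12, mean 0.88, camp variance 1.34 × the mean averaged over arms) gives 79.3% and 88.3%. With the control-arm variance it gives 82.9% and 91.0%. The stated power is reproduced closely. It concerns the primary analysis, which is not in question.

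**2. Set-up for the per-protocol ratio.** Let q be the share of commitment-type camps in the control phase and r their yield relative to freely chosen camps. The document gives neither, so both are assumptions. Suppose listed sites yield the same as freely chosen sites. Relative to a free-choice camp:

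- control-phase mean = (1 − q) + q·r
- per-protocol intervention mean = 1, because off-list camps are removed
- per-protocol ratio = 1 / ((1 − q) + q·r)

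Example: q = 0.3, r = 0.7 gives 1 / (0.70 + 0.21) = 1 / 0.91 = 1.10.

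| q | r = 0.5 | r = 0.7 | r = 1 | r = 1.5 |
|---|---|---|---|---|
| 10% | 1.05 | 1.03 | 1.00 | 0.95 |
| 20% | 1.11 | 1.06 | 1.00 | 0.91 |
| 30% | 1.18 | 1.10 | 1.00 | 0.87 |
| 40% | 1.25 | 1.14 | 1.00 | 0.83 |

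Over this grid the ratio runs from 0.83 to 1.25. It equals 1.00 only if r = 1. Applying the same camp-type exclusion in both phases gives 1.00 throughout.

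**3. Simulation check.** A small stepped-wedge simulation (40 trials per setting, van and month effects as fixed terms, quasi-Poisson) had commitment camps equally common in both phases. At q = 30%, r = 0.5 the intention-to-treat ratio was 1.01 and the per-protocol ratio 1.19, with nominal significance in 55% of runs. At q = 30%, r = 1.5 they were 1.02 and 0.88. At q = 20%, r = 1 both were 1.02. With 40 runs these show direction and rough size only.

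**4. How much is bias and how much is estimand.** Let q′ be the off-list share after the switch. The intention-to-treat ratio is ((1 − q′) + q′·r) / ((1 − q) + q·r). If q′ = q it is 1.00. If switching cuts commitment camps from 30% to 10% with r = 0.7, it is (0.90 + 0.07) / 0.91 = 1.07, a real effect of the policy. At q′ = 0 it reaches 1.10, the per-protocol value. So the per-protocol ratio can be read as the effect of full adherence against the usual-care mix, but only if the listed camps actually held represent those that could not be held. Camps dropped because listed sites were hard to reach are a stated reason to doubt that.

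**5. The 2-km rule.** A 2-km circle covers π × 2² = 12.57 km². The software works in polygons of 10 000 people, so the circle holds one polygon at 10 000 / 12.57 ≈ 796 people per km². At assumed densities of 5 000, 10 000 and 20 000 per km² it spans about 6, 13 and 25 polygons. At an assumed 100 per km² a circular polygon has radius √(10 000 / 100 / π) ≈ 5.6 km. If 25% or 50% of counted camps were really off the hotspot, a true 1.20 would read 1 + 0.20 × 0.75 = 1.15 or 1 + 0.20 × 0.50 = 1.10.

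**The case against.** The strongest reply is that site choice is the intervention. If conventional selection includes low-yield partner camps, replacing them with listed sites is part of what the software does, and a ratio of 1.10 in the example is the full-adherence effect. This stands in part, as step 4 shows: the spread in the table is not all bias. It does not rescue the claim, because the full-adherence reading needs the held camps to represent the unheld ones.

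Several stronger readings are tempting and not supported:

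- **That the analysis favours the software.** Nothing says partner camps yield less. If they yield more, the ratio falls below 1 and the rule hides a benefit. The off-list share after the switch is also meant to be kept to a minimum and need not equal the control-phase share.
- **That no control camps remain.** The sentence taken alone could be read so, but the Discussion identifies the excluded camps as those held independently of the recommendation.
- **That the 2-km rule is invalid.** Teams are given addresses and coordinates, so distance from the listed point fits their instructions, and vans park at or near the site. The mismatch with polygons rests on densities the document does not give, and counting off-hotspot camps as adherent dilutes the effect.
- **That a weak primary result will be presented as success.** The document says nothing of the kind.

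It can also be said that the SAP may hold the details. That covers a missing control-phase rule or adjustment. It does not cover the statement in the Discussion about what the analysis will show.

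**Conclusion.** The point holds in limited form. The per-protocol comparison is selected on one side by documented, non-random reasons, the planned model terms do not correct this, and the claim of a direct estimate should not stand. The document fixes neither the direction nor the size. The illustrative range of 0.83 to 1.25 assumes commitment-camp shares of 10–40%, yield ratios of 0.5–1.5, and listed sites no better than freely chosen ones, and part of it is a difference in estimand. At its ends it is about as large as the 20% effect the trial is designed to detect, so the label matters. The 2-km rule is a minor matter for a sensitivity analysis. This is a secondary analysis; the intention-to-treat primary analysis keeps every camp and is not affected.

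**What to change.** (a) In the Discussion, withdraw the claim that the per-protocol analysis estimates the effect directly. Call it a supportive, non-randomised comparison and state which camps it compares in each phase.

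(b) Do one or both of the following:

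- Apply the same camp-type restriction or adjustment in both phases, using the venue and community-mobilisation fields in Box 1. These fields name local doctors and local leaders but not non-governmental organisations, so they capture partner involvement only in part.
- Report an adherence-adjusted estimate on all camps, with the randomised switch month as the instrument and the van-month share of camps at listed locations as the exposure (a single camp has no counterpart in the other phase). State the exclusion restriction: switching changes yield only through holding camps at listed locations.

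(c) Keep the 2-km rule. Add a sensitivity analysis that defines adherence by the recorded site-selection method or, if the study team holds the polygon boundaries, by whether the camp lies in the listed polygon.

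Cost: wording changes and a little more analysis, mostly on data already collected. The instrumental estimate has a wider interval. On an additive scale at an assumed 70% adherence it is about 1 / 0.7 = 1.43 times as wide as the intention-to-treat interval. Sample size and primary analysis do not change.
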